## Abstract

Chronic widespread pain (CWP) is highly prevalent among minoritized adults with clinical obesity, and symptom management is challenging. Weight loss via bariatric surgery is often recommended to improve musculoskeletal pain. However, there is significant variation in pain trajectories following bariatric surgery, and the impact of weight loss on movement-evoked pain is largely unknown. The current study aims to systematically characterize and quantify longitudinal changes in pain at rest and movement-evoked pain up to 6 months post-surgery, and to determine whether pain modulatory mechanisms, joint motion, and mechanical loading biosignatures mediate the relationship between weight loss and pain change. This study protocol details the research methodologies and procedures for a prospective observational cohort study of 60 individuals undergoing bariatric surgery for weight loss. Participants will complete questionnaires, anthropometric measurements, clinical and experimental pain testing, functional testing, and a standardized movement testing battery to assess joint motion and mechanical loading using camera-based motion capture before and at 3 and 6 months post-bariatric surgery. Generalized linear mixed models to assess the significance of changes in PAR, MEP, and all patient-reported outcome measures. Reduced models will treat the main effect of time as a fixed factor, and intra-individual repeated measures as random effects. Ethics and dissemination: This study protocol has been registered as an observational study with ClinicalTrials.gov (NCT0675386), version #1, in the United States and has been approved by the NYU Langone Health Institutional Review Board (IRB#: i21–01652) and the New York City Health + Hospitals/Bellevue Research Office (Bellevue Study ID #: STUDY00003739). Study results will be published in peer-reviewed journals and presented at national and international conferences and community events.

## Introduction

Chronic pain and obesity are interrelated, highly prevalent conditions that disproportionately affect minoritized populations. Racial disparities in pain burden and restricted access to effective pain management persist(1). Concomitantly, non-Hispanic Black/African-American (NHB) and Hispanic/Latino/a/X/e adults have obesity rates of 40% or higher in the United States(2). Globally, over 2 billion adults are classified as overweight or having preclinical or clinical obesity (BMI > 30)(3), with an estimated 3.8 billion projected by 2050(4). The global economic burden of musculoskeletal conditions associated with higher BMI amounts to approximately $180.7 billion, affecting both high- and low-income countries, though regional differences exist(5). Furthermore, weight bias and perceived healthcare discrimination contribute to pain mismanagement(6). These issues, along with healthcare provider biases about pain reports(7, 8), frequently worsen pain for people with higher BMI or clinical obesity and lead to costly delays in seeking care(9). Therefore, understanding mechanisms of disparity in chronic musculoskeletal pain among minoritized adults with clinical obesity and higher BMI is crucial to the advancement of pain and obesity research, the promotion of health justice, and the mitigation of the global economic healthcare burden of pain.

Chronic widespread pain (CWP) is a subtype of persistent primary musculoskeletal pain (ICD-11 code)(10) characterized by pain at multiple anatomical sites, involving at least four regions and three quadrants of the body, lasting for at least three months(11, 12). CWP is a core symptom of regional and chronic overlapping pain conditions like knee osteoarthritis, persistent non-specific low back pain, and fibromyalgia(13). There are racial and gender-based disparities in CWP, specifically fibromyalgia syndrome (FMS), that are likely a consequence of underdiagnosis despite meeting ACR 2016 diagnostic criteria and greater symptom severity (14). Managing CWP is notoriously challenging, and recommended management strategies often include a combination of multimodal non-pharmacological interventions (15–17). However, there is a notable underrepresentation of minoritized adults with CWP conditions in clinical trials(18). Movement-evoked pain (MEP), musculoskeletal pain experienced during active and passive movement, is more intense than pain at rest (PAR)(19, 20). Moreover, MEP is a key driver of disability in NHB adults(21). Importantly, body size and clinical obesity influence the chronicity and progression of widespread musculoskeletal pain(22). As a result, weight loss is frequently recommended for CWP.

### Study Objectives

The primary aims of this study are to systematically characterize and quantify longitudinal changes in pain at rest (primary outcome) and MEP (secondary outcome) up to 6 months following bariatric surgery. Additionally, the study aims to quantify longitudinal changes in pain modulation and joint movement biosignatures at 6 months post-bariatric surgery. An exploratory, tertiary aim is to determine whether pain modulatory mechanisms, joint motion, and mechanical loading biosignatures mediate the relationship between weight loss and changes in pain. The working hypotheses for this study are: 1) pain at rest and MEP will demonstrate clinically significant reductions post-bariatric surgery; 2) nociceptive processing and joint biomechanics will improve following surgery; and 3) modifications in nociceptive processing and joint movement biosignatures will mediate the association between weight loss and pain reduction. The following narrative describes the study protocol.

## Materials and methods

All information is presented in accordance with the Standard Protocol Items: Recommendations for Interventional Trials – Outcomes 2025 Checklist(37–39). The study is registered with ClinicalTrials.gov (NCT0675386).

### Patient and public involvement

Patient advocates on the NYU Langone Clinical and Translational Science Institute (CTSI) Patient Advisory Council for Research (PACR) were directly consulted on study design, recruitment strategies, and compensation structure for study participation prior to data collection. Patients who were eligible for bariatric surgery and who also had chronic widespread pain were not directly consulted on study design and research methodologies.

### Study Design

The study will employ a prospective, quasi-experimental observational cohort study design.

### Study Setting

Prospective participants will be recruited from two bariatric surgery and weight management clinical sites in New York City, NY, USA. Patients will be recruited in person and by telephone from New York City Health + Hospitals/Bellevue Hospital Center (NYC H+H/Bellevue) and NYU Langone’s Weight Management Program. Prospective study participants will be recruited during bariatric surgery scheduling. Study recruitment began on August 1, 2023. The projected end of the recruitment period will be March 1, 2028. Recruitment and data collection are ongoing. The NYC H+H/Bellevue Center for Obesity & Weight Management is a multidisciplinary program that offers comprehensive weight management services within a publicly funded academic medical center. Patients receive a suite of medical, surgical, and lifestyle modification weight management options in consultation with primary care physicians, psychologists, nutritionists, and bariatric surgeons, and will continue to receive this standard of care throughout the study. The research study team will include clinician-scientists (2 MDs, 1 physical therapist, 2 PhD research trainees who are physical therapists, 2 research assistants), biostatisticians, and 4 research consultants with expertise in weight management, obesity science, and pain neuroscience. The research assistants will be trained by the physical therapist in all data collection methods, and inter-rater reliability will be determined as part of the training protocol. The research team members who will recruit and obtain informed consent are fluent in conversational English and Spanish.

### Human Research Protections

The study has been approved by the NYU Langone Health Institutional Review Board (IRB # i21–01652) and the New York City Health and Hospitals/Bellevue Hospital Center Office of Research (Bellevue Study ID #: STUDY00003739). All research study personnel have completed human subjects research training modules for NYU Langone Health and NYC H+H/Bellevue Hospital Center before recruitment or data collection activities. Research personnel will report unanticipated problems and adverse events to the bariatric surgeon of record, the NYU Langone IRB, and the NYC H+H/Bellevue Hospital Center Office of Research.

### Participant Eligibility Criteria and Recruitment

Written informed consent will be obtained in English or Spanish at the NYC H+H/Bellevue Bariatric Surgery Clinic (primary site) and NYU Langone Tisch Bariatric Clinic (secondary site) prior to study enrollment.

#### Study Eligibility Criteria

Study participants will be new patients from the NYC H+H/Bellevue or NYU Tisch Weight Management Clinics. We will recruit participants who self-identify as Hispanic/Latino/a/X/e and/or NHB based on the 2020 U.S. Census racial categories(40). Demographic information will be collected using the NIH PhenX Toolkit Common Data Elements(41). Participants can select nationality and cultural affiliation, country of origin, gender identity, sex assigned at birth, sexual orientation, current address, household income, and educational level.

Inclusion criteria for study participation are adults 18 to 75 years of age who have elected to undergo bariatric surgery, have pain of at least 3 out of 10 on the Brief Pain Inventory (BPI) Severity subscale at 3 or more anatomical sites, are literate and numeracy fluent in conversational English or Spanish, and have the cognitive capacity to consent to study participation. The main study exclusion criteria are patients who either have pain at less than 3 anatomical sites or pain intensity less than 3 out of 10 on the BPI upon screening, are undergoing revision of a previous bariatric surgery, have localized, acute pain within 6 weeks of study enrollment, or are unable to walk a minimum of 10 feet (3.05 m) unassisted or using a single point cane.

Study eligibility will be determined at 1 of 3 phases of study recruitment. Participants will be approached by a member of the research study team during their initial visit to both study sites and asked if their preferred conversational language is English or Spanish. Research study personnel will then briefly introduce participants to the study. Participants will be informed that their participation in the study is strictly voluntary and will not affect the standard of care before or after bariatric surgery. They will also be informed that they are not financially responsible for any data-collection costs and will be compensated for their participation. If the patient agrees, a screening questionnaire will be administered to participants in English or Spanish. If the patient is eligible for study participation, a research team member will contact them by telephone to explain the study protocol in greater detail and to schedule the first of three data collection sessions (Visit 1). Research personnel will invite participants to meet with the principal investigator to address additional questions or concerns in English or Spanish.

Participants will be enrolled in the study after obtaining written informed consent in English or Spanish. Consent will be obtained in person or remotely using a secure electronic platform. After obtaining written informed consent, study participants will be further screened in person at Visit 1 for neurological, sensory, or motor impairments not assessed during the first 2 phases. If participants demonstrate neurological, sensory, or motor impairments during this examination, they will be deemed ineligible to continue in the study.

### Participant Protections

This is a prospective, quasi-experimental observational study, and all participants will receive standard-of-care bariatric surgery services throughout the study period (42). Study participants will be contacted by telephone, text, and email within 48 hours of data collection to monitor for adverse events associated with pain and movement tests that may elicit discomfort. Clinical pain will be assessed 3 months after bariatric surgery via surveys and telephone contact with participants to gather information on surgery type, current medications, and other relevant health-related issues. An independent study advisory board that is independent from the funder or sponsor will review data collection procedures and evaluate reports of study-related adverse events, such as a worsening of clinical pain or physical function, provided by study personnel. A data monitoring committee appointed by the funder or sponsor is not required because the current study is not a randomized clinical trial. Patient confidentiality will be ensured through multiple methods, including, but not limited to, study ID numbers on forms containing protected health information (PHI) or protected identifying information (PII), and data storage on encrypted servers.

### Sample Size Determination

The sample size needed to achieve the study's primary aim was determined using extant clinical data from a longitudinal observational cohort study of surgical weight loss(43) (NYU IRB# 16–01995). The primary objective of the study is to characterize and quantify changes in pain at rest (PAR, primary outcome) and MEP (secondary outcome). Power analyses were conducted based on the anticipated within-person mean change in pain at rest from baseline to 6 months post-surgery (primary outcome). Additionally, the clinical assumptions supporting our sample size determinations were the minimum clinically important difference (MCID) for the Brief Pain Inventory (BPI) average pain (2.1 points) and BPI Severity (2.2 points) scores in adults with fibromyalgia (44). The sample size was calculated to detect a Cohen’s d of 0.50 for BPI Severity scores at 3 months, based on a secondary analysis of the parent study cohort, which revealed a sharp reduction in pain intensity ratings in a stratified cohort of NHB and/or Hispanic/Latino/a/X/e adults(22). We considered a 1-point reduction in pain interference at 6 months to be conservative, as proposed in the Initiative on Methods, Measurement, and Pain Assessment in Clinical Trials (45). The sample size calculation assumed a Type I error rate of 2.5% to account for multiple comparisons and 90% power. We estimated a sample size of 50 using a two-sided paired t-test. Thus, we will recruit at least 60 participants to account for a 20% attrition rate, although attrition in the target study population may be higher(46).

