### Pain Measurement and Assessment

#### Pain Intensity at Rest (PAR)

Pain intensity at rest (PAR) will be evaluated using the Numeric Pain Rating Scale (NPRS) and the Brief Pain Inventory – Short Form (BPI-SF).

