#### Brief Pain Inventory – Short Form (BPI – SF)

The BPI-SF is a 9-item self-assessment that measures pain intensity, interference with physical functioning, and pain location(59). The BPI-SF Pain Severity and Pain Interference subscales feature anchors from 0 (“no pain”) to 10 (“Pain As Bad As You Can Imagine”), and the subscale score is the mean of the four items. The BPI-SF Pain Interference subscale is the mean of 7 items. The BPI-SF has been validated in Spanish (60) and in adults undergoing bariatric surgery (61, 62). The BPI-SF assesses pain domains recommended by the Initiative on Methods, Measurement, and Pain Assessment in Clinical Trials (IMMPACT)(45, 63). Pain at rest will be measured before vital signs and anthropometric measurements are taken.

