The movement testing battery will include bilateral seated knee extension, overground walking, picking up a weight from a step (object pick-up task), and a bilateral step-down task (Figure 3). Participants will be given scripted instructions in either English or Spanish on how to perform each movement task and will complete one practice trial before recording. Participants will perform knee flexion and extension while sitting on a stool for the seated knee extension task. The stool will be adjusted to the participants’ height to maintain 90 degrees at knee flexion with the thighs parallel to the floor. Two trials will consist of 5 repetitions per leg, and the average of each trial will be used in all statistical analyses. For the walking task, participants will perform 5 trials over a 13 ft (396.2 cm) walkway at their self-selected gait speed. Gait speed will be included as a covariate in statistical analyses because it is associated with weight or BMI(111). The average of 3 trials will be used for statistical analyses. For the object pick-up task, participants will pick up a 5-lb (2.27 kg) weight from a 6-inch (15.2 cm) step and return it to its original position. There will be 3 trials of this task, and the average will be included in statistical analyses. For the step-down task, participants will be asked to ascend and descend a 6-inch step with the same lower extremity. There will be 2 trials for each lower extremity, and the average across trials will be included in the statistical analyses. The primary kinematic variables to be analyzed are peak knee flexion and extension, and peak trunk flexion and extension, across all movement tasks. The primary kinetic variables to be analyzed are peak knee and trunk extension moments (N · m/kg). We will include additional kinematic and kinetic variables in our exploratory analyses. Participants will rate their PAR before the practice trial. Upon completion of the last trial of the movement task, participants will be asked to rate their pain immediately and 1 minute after task completion.

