### Primary and Secondary Aims

The study's primary aim is to systematically characterize and quantify changes in PAR 6 months post-surgery. The secondary aim is to quantify changes in MEP at the same study endpoint. NPRS pain ratings will be averaged, and change scores (PAR _baseline_ – PAR _6M_) will be calculated at baseline and 6M post-surgery (primary study endpoint). Aggregate MEP scores will be analyzed at baseline and at 6 months post-surgery. Since data will be correlated due to repeated measures of pain-related outcomes within the same participant, we will apply mixed-effects models at the record level to evaluate longitudinal changes in PAR after bariatric surgery(114). This model accounts for differences in PAR slope before and after a specified time event. Previous studies from our group indicate differences in PAR slope between baseline and 3 months post-bariatric surgery, and between 3M and 24 months post-surgery(115).

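### The sample size and 90% power are calculated for BPI Severity at 3 months, but the primary change score is averaged NPRS at 6 months, so the power is not shown for the primary test

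*Protocol article*

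**What the plan says.** All references are to the protocol article.

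- **Sample Size Determination, stated basis.** The power analysis is said to rest on the "within-person mean change in pain at rest from baseline to 6 months post-surgery (primary outcome").
- **Sample Size Determination, calculation.** The sample size was then computed for a Cohen's "d of 0.50 for BPI Severity scores at 3 months", with a two-sided paired t-test, type I error of 2.5% and 90% power, giving 50. The section also cites MCIDs of 2.1 points (BPI average pain) and 2.2 points (BPI Severity), and a 1-point reduction in pain interference at 6 months. It gives no SD of change linking any of these to d.
- **Pain Intensity at Rest (PAR).** PAR "will be evaluated using the Numeric Pain Rating Scale (NPRS) and the Brief Pain Inventory" Short Form. Neither is named as the primary measure.
- **Primary and Secondary Aims.** "NPRS pain ratings will be averaged, and change scores" are formed between baseline and 6 months, the primary study endpoint. Longitudinal change in PAR is analysed with mixed-effects models. The section also reports, from the group's own earlier work, "differences in PAR slope between baseline and 3 months post-bariatric surgery, and between 3M and 24 months post-surgery".
- **Study Objectives.** The first hypothesis is that "pain at rest and MEP will demonstrate clinically significant reductions post-bariatric surgery".
- **Timing of the rest assessment.** The BPI-SF section says: "Pain at rest will be measured before vital signs and anthropometric measurements are taken". The Data Collection overview instead puts blood pressure, skin temperature and oximetry first, then pain at rest, then anthropometry. It places the questionnaires after the sensory testing.

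**The concern.** A power statement is useful only if it describes the test that will be done. Here the sizing and the analysis differ in both instrument and time point, and the sizing section disagrees with itself on the time point. A reader who takes the 90% at face value will attach it to the 6-month primary comparison, for which the protocol gives no effect size, SD or power.

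The instrument is also open. With two measures under one primary outcome and neither ranked, the measure that is emphasised could be settled after the data are seen.

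A second, separate matter is interpretation. The hypothesis speaks of clinically significant reductions, while the sizing is for a test against zero change at a standardised effect that is never expressed in points.

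**Working it through.** **1. Reproduce the stated figure.** Inputs from Sample Size Determination: two-sided alpha 0.025, power 0.90, d = 0.50, paired test.

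Normal approximation: n = ((z(0.9875) + z(0.90)) / d)² = ((2.2414 + 1.2816) / 0.50)² = 49.6, rounded up to 50. This matches.

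The exact noncentral t calculation gives 53, and 88.5% power at n = 50. The difference is small, and the stated 50 is a fair result for the inputs used.

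**2. What the inputs describe, against what is analysed.**

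| | Stated basis of power | Calculation of n | Primary change score |
|---|---|---|---|
| Instrument | PAR (NPRS and BPI-SF) | BPI Severity | NPRS, averaged |
| Time | 6 months | 3 months | 6 months |

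The calculation matches the primary change score on neither row.

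**3. How much the carry-over matters.** The documents give no 6-month NPRS effect, so no single corrected sample size can be computed. For a range of assumed values of d at 6 months (exact paired t, two-sided alpha 0.025):

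| Assumed d | n for 90% power | Power at n = 50 |
|---|---|---|
| 0.50 | 53 | 88.5% |
| 0.45 | 64 | 80.5% |
| 0.40 | 81 | 69.6% |
| 0.35 | 104 | 56.7% |
| 0.30 | 141 | 43.1% |

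A d above 0.50 would give more than 88.5%. The direction is unknown.

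**4. The MCID in points.** The change implied by d is d × SD of change, and the SD is not given.

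- d = 0.50 equals 2.2 points only if SD = 2.2 / 0.50 = 4.4. It equals 2.1 points only if SD = 2.1 / 0.50 = 4.2.
- For assumed SDs of 2, 2.5 and 3, d = 0.50 is 1.0, 1.25 and 1.5 points. The ends of that range are 1.0 / 2.2 = 45% and 1.5 / 2.2 = 68% of the 2.2-point MCID.
- Detecting a true 2.2-point change against zero with 90% power needs 13, 19, 26 or 34 participants for SDs of 2, 2.5, 3 or 3.5. Sizing for an effect below the MCID therefore does not weaken the test for an MCID-sized change.

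**The case against.** Several points on the other side are sound.

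- **BPI Severity belongs to the construct.** The PAR section lists the BPI-SF as a PAR measure, so sizing on it is not sizing on a foreign outcome. This stands, but it confirms that two measures share one primary outcome, and the change score in the aims section is built from the NPRS.
- **The time point is fixed.** A reader might infer that 3 or 6 months could be chosen later. The documents do not support that: Sample Size Determination, Data Management and Security, and the aims section all set 6 months. Three months enters only as the source of the effect size, so only the instrument is open.
- **Different slopes do not mean a smaller 6-month effect.** A steep early fall followed by a flatter course could leave the 6-month change equal or larger. This stands. The supported statement is that the carry-over is unjustified, not that power is known to be lower.
- **The targeted effect cannot be called well below the MCID.** Without an SD of change this is conditional, and the gap closes at SDs of 4.2 to 4.4. In any case it bears on interpretation, not on power.
- **Averaging.** Under Motion Analysis, "Participants will rate their PAR before the practice trial", which comes after the experimental pain tests, so a reader might infer that the averaged NPRS mixes early and test-provoked ratings. No section says that these pre-task ratings enter the primary score; they read naturally as each task's reference value. What stands is that the NPRS is a single item and the ratings to be averaged are not identified.

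Finally, this is a single-cohort observational study meant to characterise change, and a test is not its only product. That lowers the stakes but does not make the power statement apply to the primary endpoint.

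**Conclusion.** The point holds. The sizing section contradicts itself on the time point, and its calculation differs from the primary change score in instrument and time. The stated 90% power (88.5% exactly, at n = 50) is therefore shown for BPI Severity at 3 months and not for the 6-month primary test. The calculation itself is not wrong.

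The size of the discrepancy cannot be fixed from the documents. Over assumed 6-month effects from 0.50 down to 0.30, power with 50 participants runs from 88.5% to 43.1%; a larger effect would raise it.

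The MCID remark is conditional on the SD of change. At any SD below 4.4, d = 0.50 is less than 2.2 points, so rejecting zero change would not by itself support the hypothesised clinically significant reduction.

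**What to change.** 1. Name one primary PAR measure at 6 months. BPI-SF Severity is the natural choice, because eligibility, the 2.2-point MCID and the sizing already use it; naming the NPRS would also remove the contradiction. Make the other measure supportive.
2. Take the primary measure at the session-start rest assessment, before sensory and movement testing. Reconcile the Data Collection overview with the BPI-SF section on whether this comes before or after vital signs, and state that the BPI-SF is not completed with the later questionnaires if it is primary. If the NPRS is kept in any role, say which ratings are averaged.
3. Restate d, with its assumed SD of change, and the resulting power for that measure at 6 months. Remove the 3-month basis, or justify its use for 6 months.
4. Report the mean change with its confidence interval alongside the MCID, and the proportion improving by at least 2.2 points if BPI Severity is primary.

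The cost is wording in the protocol and analysis plan and alignment of the registry entry. Both instruments are already collected, so no new measure is needed. The downsides are that one PAR measure becomes supportive and that the restated power may be less favourable than 90%. Recruitment is planned to run until March 2028, so the change can still be made before the final analysis.

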There are also limitations. Selection bias refers to systematic factors that can result in the misrepresentation or underrepresentation of the relationship between exposure and outcome(s) in a target study population(125), and can occur at any point from study enrollment to analysis(126). Study attrition among minoritized populations poses a challenge for observational longitudinal studies and may contribute to selection bias. Limited work-schedule flexibility, difficulty finding childcare, long commutes, and strained financial resources significantly hinder retention in weight-loss studies (127). Based on our previous work, we estimate a study attrition rate of 20–40% at the 6-month follow-up (22, 34). We acknowledge potential threats to the study's internal validity, such as bias and confounding, that may arise directly or indirectly from study attrition (128). The research team will mitigate attrition bias by approaching and screening all eligible patients for bariatric surgery. Since the majority of patients attending the bariatric surgery clinics at both sites are Spanish-speaking or bilingual (fluent in English and Spanish), our research team will communicate with prospective participants in their preferred language for receiving health information. Additionally, we will continually evaluate and implement best practices for recruiting and retaining study participants in weight management studies(129). Measurement bias can arise from systematic errors in data collection and from respondents’ understanding of and willingness to answer survey items, which may influence scoring and the clinical interpretation of the measurement tool (130). To mitigate measurement bias, we will use validated surveys in participants’ preferred language. Additionally, the research team will review participant surveys upon request and will periodically perform data validation to monitor for missing item responses and ensure data quality. A better understanding of the primary driver(s) of CWP dimensions and the key drivers of the intervention response to surgical weight loss could help identify pain responders and non-responders after weight loss who would significantly benefit from adjuvant analgesic or non-pharmacological interventions for continued pain relief during the postsurgical period.

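### Recruiting 60 does not cover the stated 20% attrition (48 remain against the 50 required), and the stated 90% power is not met anywhere in the protocol's own 20–40% attrition range

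*Protocol article*

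**What the plan says.** All the sizing inputs are in the Sample Size Determination section of the protocol article. The effect is a Cohen's "d of 0.50 for BPI Severity scores at 3 months". On error rates: "The sample size calculation assumed a Type I error rate of 2.5% to account for multiple comparisons and 90% power". The result: "We estimated a sample size of 50 using a two-sided paired t-test". The recruitment target follows: "we will recruit at least 60 participants to account for a 20% attrition rate", and the same sentence adds "although attrition in the target study population may be higher", without a figure.

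The limitations paragraph of the Discussion does give a figure, based on the team's previous work: "we estimate a study attrition rate of 20–40% at the 6-month follow-up". Data Management and Security names the 6-month visit (Visit 3) as the primary study endpoint, so this attrition applies to the primary outcome. The document gives no second target and no power for losses above 20%.

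**The concern.** To end with n evaluable participants after losing a fraction a, one must enrol n/(1 − a). The protocol's 60 matches n × (1 + a) instead, which always falls short. The target therefore misses its own requirement at the attrition rate it names.

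The larger issue is that the named rate is the lower end of the range the investigators expect. The consequences for power at the upper end are not carried into the sizing. A reader of the Sample Size Determination section would take 90% power with an allowance for attrition as a property of the design, and on the protocol's own inputs it is not. At stake is the chance of detecting the planned change in pain at rest, and how a non-significant or imprecise primary result would later be interpreted.

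**Working it through.** **Inputs.** d = 0.50, two-sided α = 0.025, power 0.90, paired t-test, 50 evaluable, 60 recruited and 20% attrition (Sample Size Determination); 20–40% attrition at 6 months (Discussion). The protocol ties d = 0.50 to the 3-month BPI Severity score; I apply it to 6-month completers, since the section says power was based on the change from baseline to 6 months.

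**Step 1: reproduce the 50.** Normal approximation: n = ((z₀.₉₈₇₅ + z₀.₉₀)/d)² = ((2.2414 + 1.2816)/0.50)² = 49.6, so 50. The stated figure reproduces. The exact noncentral-t calculation for the paired t-test gives 53 (power 88.5% at 50, 89.9% at 52, 90.5% at 53).

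**Step 2: the inflation.**
- As stated: 50 × 1.20 = 60.
- Correct: 50/(1 − 0.20) = 62.5, so 63.
- Back-check: 60 × 0.80 = 48, two below 50.
- Largest loss that still leaves 50: 1 − 50/60 = 16.7%.

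**Step 3: power across the protocol's attrition range.** Completers = 60 × (1 − a). Exact power is from the noncentral t with n − 1 degrees of freedom and noncentrality 0.50 × √n. The normal approximation is Φ(0.50 × √n − 2.2414).

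| Attrition | Completers | Power, paired t | Power, normal approx. |
|---|---|---|---|
| 20% | 48 | 87.1% | 88.9% |
| 30% | 42 | 81.6% | 84.1% |
| 40% | 36 | 74.2% | 77.6% |

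No row reaches 90% by either method. At 40% loss the Type II error is about 26% (1 − 0.742), against the planned 10%.

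**Step 4: effect detectable with 90% power** (exact paired t, two-sided 2.5%). d = 0.52 with 48 completers and d = 0.61 with 36.

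**Step 5: enrolment that would keep 90%.** From 50 evaluable: 50/0.8 → 63, 50/0.7 → 72, 50/0.6 → 84 at 20%, 30% and 40% loss. From the exact 53: 67, 76 and 89.

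**The case against.** Several points on the other side have force.

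- **The inflation slip alone is small.** It leaves 48 rather than 50 completers, and exact power falls from 88.5% to 87.1%, or 1.4 percentage points. This stands: the weight of the point lies in the 20–40% range.
- **The risk is disclosed.** The sizing sentence concedes that losses may exceed 20%, and the Discussion lists attrition as a limitation. A reader might infer that the two sections contradict each other. Strictly they do not, because 20% lies at the edge of the stated range. What remains is that the target was sized to the best case and no power is shown for the rest.
- **The target is a floor.** Recruitment runs to March 2028 and progress is reviewed every 6 months, so more than 60 could be enrolled. That is possible, but the document sets no number or rule that would restore 90%.
- **The planned analysis is a mixed-effects model** (Primary and Secondary Aims), which can use the 3-month data of participants lost by 6 months. It may recover part of the loss, and the figures above are completer figures. The gain cannot be computed from the document, and the protocol's own power statement rests on a paired t-test, which needs complete pairs.

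Two stronger readings should be resisted. A reader might infer that the 50 is itself a miscalculation. It is the correct normal-approximation answer; for the named t-test it falls 1.5 points short, which merits a note only. A reader might also infer that the neurological screen at Visit 1, after which some consented participants "they will be deemed ineligible to continue in the study", reduces the 60 further. The document gives neither a screen-failure rate nor a rule on whether the 60 is counted before or after that screen, so no such reduction can be shown.

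**Conclusion.** The point holds. Sixty enrolled does not absorb 20% attrition from a requirement of 50; 63 would be needed. With the 20–40% attrition the investigators expect at the primary endpoint, 36 to 48 participants would have 6-month data. Power for d = 0.50 at two-sided 2.5% would then be about 74–87% by the exact paired t-test (78–89% by the normal approximation), not 90%.

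This rests on exactly 60 enrolled, analysis of complete pairs only, and d = 0.50 applying at 6 months. Enrolment above 60, or information recovered through the mixed model, would improve the figures by an amount the document does not allow one to quantify. It therefore does not follow that the study cannot reach 90% power, only that the stated target and attrition do not support the claim.

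**What to change.** Keep 60 and restate the section along these lines: *60 enrolled with 20–40% attrition gives 36–48 participants with 6-month data and about 74–87% power (paired t-test, completers only) for d = 0.50 at two-sided 2.5%, or 90% power for d = 0.52–0.61; the planned mixed model using 3-month data may recover part of this loss.* Remove the statement that 60 accounts for 20% attrition at 90% power. Also note that 50 is the normal-approximation result and that the exact paired t-test needs 53.

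The cost is rewording and a less favourable stated power; no further participants are required. If the sponsor prefers to keep the 90% claim, that is a different choice. The target must then be set by n/(1 − attrition): 63 at 20% and 84 at 40% from a base of 50, or 67 and 89 from the exact 53. The section should take one route or the other, since a target of 60 and 90% power cannot both stand at the stated attrition.
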